### Data reduction and analytic plan

Data was analysed using RStudio version 1.3.1073 [49] with R version 4.0.2 [50]. As this is a pilot study, descriptive statistics and Cohen’s *d* effect sizes only are reported. Pearson’s correlation coefficients were also computed across all participants between self-report measures with measures of interpretation bias and interpretation of somatosensory sensations using the R package ‘corrplot’ [51]. Self-report measures were scored according to their published instructions. For the Ambiguous Scenarios Task, the proportion of correct comprehension questions was calculated to determine engagement with the task. Mean scores for each category of ending were calculated for each participant. The mean score for benign target endings was be subtracted from the mean score for negative endings to give an index of biased interpretation, as in previous use of the Ambiguous Scenarios Task [52]. A positive interpretation bias index indicates pain-related interpretation bias.

Ambiguousscenariosindex=TN−TB

Where *TN* =  mean score for target negative endings and *TB* =  mean score for target benign endings.

For the Incidental Learning Task, trials with incorrect or no response were excluded (learning phase: 1.39%, testing phase: 1.54%). Histograms and boxplots showed that response times less than 200ms or greater than 800ms were outliers, so these were removed (learning phase: 1.00%, testing phase: 1.08%). Response times more than three standard deviations outside each participant’s mean response time were excluded (learning phase: 1.70%, testing phase: 1.54%). The congruency effect was calculated with data from the learning phase. A positive congruency effect indicates a faster response when the dot appears on the predicted side of the screen, indicating that the contingency has been learnt.

Congruencyeffect=RTi−RTc

Where *RTi* =  mean response time on incongruent trials and *RTc* =  mean response time on congruent trials. The IB index was calculated from response times in the test phase, as in previous research [18,53]. A positive index indicates pain-related interpretation bias.

Interpretationbiasindex=RTn−RTp

Where *RTn* =  mean response time to targets in the location associated with neutral words and *RTp* =  mean response time to targets in the location associated with pain words.

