### Correlational analyses

Anxiety sensitivity was positively associated with unpleasantness ratings for stimuli at 60% (*r* = .51) and 80% (*r* = .51) of the pain threshold. State anxiety was positively associated with intensity ratings for stimuli at 80% (*r* = .48), and 100% (*r* = .48), of the pain threshold, as well as with unpleasantness ratings for stimuli at 60% (*r* = .72), 80% (*r* = .75) and 100% (*r* = .77) of the pain threshold. Trait anxiety was positively associated with intensity ratings for stimuli at 140% (*r* = .48) of the pain threshold, and with unpleasantness ratings for stimuli at 60% (*r* = .61), 80% (*r* = .55), 100% (*r* = .59), 120% (*r* = .56), and 140% (*r* = .54) of the pain threshold. Anxiety sensitivity was positively associated with the proportion of pain sentences generated (*r* = .57). Additionally, scores on the test phase of the Ambiguous Scenarios Task and Sentence Generation Task were correlated (*r* = .68).

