Based upon these findings and results from the broader literature, the following modifications have been made to the experimental protocol for the main investigation. First, the primary outcome of interpretation of ambiguous somatosensory sensations will be performed immediately following CBM-I, with assessment of post CBM-I cognitive biases performed after this. This will eliminate the possibility that assessing post-CBM-I cognitive biases reduces the training effect. Second, assessments of pain-related attentional bias and memory bias will also be conducted following CBM-I. Pain-related biases in attention (e.g., [57–68]) and memory (e.g., [45,69–74] have been frequently explored by our research group and others across a range of populations and using a range of paradigms, and their inclusion in the protocol will enable an assessment of the inter-relatedness of different forms of cognitive bias as predicted by theoretical models such as the Threat Interpretation Model of Pain [75] and the Integrated Contextual-Functional Framework [76]. Third, due to the small between-groups effect size (*d* =  -0.05) in the pilot study, the Incidental Learning Task will not be included (and which will provide time for assessments of attentional and memory bias). Fourth, in addition to ambiguous hot sensations, an assessment of interpretation of ambiguous cold sensations will also be conducted, as research suggests people are more sensitive to cold stimuli than hot stimuli [77,78], perhaps due to a greater overall density of cutaneous cold thermoreceptors than warm receptors [79]. Fifth, research has suggested intolerance of uncertainty is associated with higher experimental pain intensity ratings [80]. The Intolerance of Uncertainty Scale-12 Item [81] measure will therefore be added to the questionnaire battery in order to explore associations between intolerance of uncertainty and interpretation of ambiguous somatosensory sensations.

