### Procedure

The procedure for this study is shown in Fig 4. Participant ID numbers will be randomly assigned to the benign or pain modification group before data collection begins. After having read the information sheet and signed the consent form, participants will first complete the questionnaire battery. Following this, participants will complete the pain-threshold measurement task to assess their hot and cold pain thresholds. Next, participants will complete the Ambiguous Scenarios Task aiming to modify their biases towards pain-related or benign interpretations of ambiguous stimuli, according to their randomised group. Immediately following this, participants will complete the Interpretation of Ambiguous Sensation Task. All participants will then complete the battery of cognitive bias tasks. The test phase of the Ambiguous Scenarios Task will be completed first. The order of the sentence generation task and visual-probe task will be randomised and counterbalanced across participants, with the free recall memory bias task conducted last. Lastly, those randomised to the pain modification condition will complete the bias repair task. Participants will complete the study in a single session lasting approximately two hours minutes. Following completion of the study, participants will be thanked and debriefed. The entire experiment will take approximately 120 minutes to complete.

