Descriptive statistics will be computed for demographic characteristics, self-report measures (scored according to their instructions), cognitive bias task scores (Ambiguous Scenarios Task test phase, Sentence Generation Task, Visual-Probe Task and free recall task) and responses on the Interpretation of Ambiguous Somatosensory Sensations Task. Differences between the benign and pain modification groups will be conducted using independent samples *t*-tests and mixed-design ANOVAs where appropriate. Should any statistically significant differences be observed between groups on demographic or self-report measures, analyses will be conducted controlling for these (e.g., Analysis of Covariance). Pearson’s correlation coefficients will be conducted between outcomes on the self-report measures, cognitive bias scores and interpretation of ambiguous sensations ratings. As thermal pain sensitivity is associated with age (e.g., [88–90]), Pearson’s correlation coefficients will also be computed between age and interpretation of ambiguous sensations ratings. Should these be statistically significant, then age will be controlled for as a covariate where appropriate in the statistical analyses. The moderating effects of visual imagery and intolerance of uncertainty on the association between group and interpretation bias scores from the Ambiguous Scenarios Task will be investigated using linear multiple regression models. Similarly, linear multiple regression models will be used to test the effect of group on interpretation bias measures while controlling for other variables that differ between groups.

Data from the Ambiguous Scenarios Task, Sentence Generation Task and ISSA will be processed as discussed above for the pilot study. The only difference is that for the Sentence Generation Task, two raters will independently and blindly categorise participant response sentences as either pain-related (e.g., *He had a pressing pain in his head*) or benign (e.g., *The boy was pressing the buttons in the lift*). The initial inter-rater agreement will be computed, and any disagreements between raters will be discussed in order to reach consensus (involving a third independent member of the research team if necessary).

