Overall, the intended aims of the pilot study were met, providing important insights allowing us to make modifications to the experimental design in preparation for the main study. Additionally, our research team (e.g., [3,44,45]) and others (e.g., [75,92–94]) are increasingly calling for research exploring the interrelationships between different forms of cognitive bias. The combined cognitive bias hypothesis proposes that different forms of cognitive bias influence and interact with each other, and these interactions may have a greater impact on maintaining emotional disorders than individual biases in isolation [95]. Specifically for pain, the Integrated Contextual-Functional Framework [76] posits that pain-related biases in attention, interpretation, and memory arise from shared contextual and motivational factors. These biases are likely interconnected and may amplify each other. The protocol detailed here will not only allow us to investigate the effects of pain-related CBM-I on the interpretation of ambiguous somatosensory stimuli, but will also allow us to explore the interrelationships between attentional, interpretation and memory biases for symbolic pain-related stimuli. The results of this research with pain-free individuals will likely inform future research on the transition from pain-free states to acute pain, and subsequently to chronic pain in some individuals. Additionally, the novel ISSA paradigm we developed can be used to further explore the zone of uncertainty across other patient populations who may interpret or evaluate ambiguous bodily sensations differently compared to healthy individuals.

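### Correlations among post-training bias scores and ISSA ratings carry no term for randomised group, so they cannot separate linked biases from a shared training effect

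*Protocol article*

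**What the plan says.** The main study's Data reduction and analytic plan states that Pearson's "coefficients will be conducted between outcomes on the self-report measures, cognitive bias scores and interpretation of ambiguous sensations ratings". No group term, stratification or partialling is attached. The adjustments named in that section are for group differences on demographic or self-report measures, for age, and within regressions of interpretation bias on group.

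The pilot's section of the same name is explicit about pooling: Pearson's "coefficients were also computed across all participants between self-report measures with measures of interpretation bias and interpretation of somatosensory sensations". The pilot's Correlational analyses then report that "scores on the test phase of the Ambiguous Scenarios Task and Sentence Generation Task were correlated" (r = .68).

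Two passages give these data a purpose. Insights for the main experimental study says that including the attention and memory tasks "will enable an assessment of the inter-relatedness of different forms of cognitive bias as predicted by theoretical models". The Discussion says the protocol will "allow us to explore the interrelationships between attentional, interpretation and memory biases for symbolic pain-related stimuli".

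On timing, the main study's Procedure places the questionnaires and thresholds first, then CBM-I, then the ISSA, after which "All participants will then complete the battery of cognitive bias tasks". Aims and hypotheses predicts higher values in the pain arm for ISSA ratings and for interpretation, attentional and memory bias.

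**The concern.** Every bias score and ISSA rating is taken after randomised training that is meant to push the arms apart on all of them. Randomised group is then a common cause of both members of each such pair. If training moves two measures, people in the pain arm tend to be high on both and people in the benign arm low on both. The combined sample shows a correlation even when the two are unrelated inside each arm. The better the training works, the larger this component.

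At stake is how the exploratory question on inter-relatedness is read. A significant pooled coefficient could mean that people with more of one bias have more of another, or only that the same training shifted both. The coefficient alone cannot tell these apart. The group comparisons on the primary outcomes are not affected.

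**Working it through.** **Inputs from the protocol article**
- Design effect f = 0.244, so d = 2f = 0.488 for two equal groups; α = .05; power 0.80; N = 134 (main study, Participants). No allocation ratio is stated; 67 per arm is assumed.
- Ambiguous Scenarios d = 1.03; Sentence Generation |d| = 1.02 as printed (pilot, Assessments of interpretation biases).
- ISSA at 80% of threshold: intensity d = 0.82, unpleasantness d = 1.00 (pilot, Table 3).
- Pilot correlation of Ambiguous Scenarios with Sentence Generation: r = .68, 9 per arm.
- No effect size is given for the visual-probe or free-recall tasks.

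**Step 1: the plan's own figure.** Using the noncentral F with 1 and N − 2 degrees of freedom and λ = f²N = 0.244² × 134 = 7.98, power is 0.8006 at N = 134 and 0.7977 at N = 133. The stated 134 is reproduced. The article gives no figure for the correlations.

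**Step 2: check the pilot effects.** From the printed means and SDs:
- Ambiguous Scenarios: (0.44 + 4.44) / √((4.82² + 4.61²)/2) = 1.03.
- Sentence Generation: (0.28 − 0.15) / √((0.10² + 0.17²)/2) = 0.93, against 1.02 printed. Both values are carried forward.

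**Step 3: correlation created by pooling.** With zero within-group correlation and equal arms,

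r = (d₁d₂/4) / √((1 + d₁²/4)(1 + d₂²/4)).

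For d = 1.03 and 1.02: 0.2627 / √(1.2652 × 1.2601) = 0.2627 / 1.2627 = .208.

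**Step 4: how often it is significant.** The two-sided critical |r| at N = 134 is .170. Rates come from 40,000 simulated trials per row, with normal data and 67 per arm.

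| Pair | d₁, d₂ | Pooled r | p < .05, pooled |
|---|---|---|---|
| Ambiguous Scenarios, Sentence Generation (printed d) | 1.03, 1.02 | .21 | 69% |
| Same, d from means and SDs | 1.03, 0.93 | .19 | 63% |
| Ambiguous Scenarios, ISSA unpleasantness at 80% | 1.03, 1.00 | .20 | 67% |
| Ambiguous Scenarios, ISSA intensity at 80% | 1.03, 0.82 | .17 | 53% |
| Ambiguous Scenarios, outcome at design effect | 1.03, 0.488 | .11 | 24% |
| Both at design effect | 0.488, 0.488 | .06 | 10% |
| Ambiguous Scenarios, assumed small effect | 1.03, 0.2 | .05 | 8% |
| One measure not moved by training | 1.03, 0 | .00 | 5% |

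Partialled on group, the mean r is .00 and the rate is 4.8% to 5.3% in every row.

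**Step 5: the pilot correlation.** Inverting the formula with the pilot effects, the within-group value is .68 × 1.2627 − 0.2627 = .596. Depending on which Sentence Generation d is used and whether the small-sample term is included, it lies between .585 and .604. Group therefore accounts for only a small part of the pilot r.

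**The case against.** **Pooling is inferred.** The main-study plan does not repeat that all participants are combined; that phrase describes the completed pilot. This stands as a limit. But the stated method has no group term, the precedent is pooled, and none of the listed adjustments removes group from a correlation between two post-training outcomes. Followed as written, the plan gives pooled coefficients.

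**No hypothesis rests on these correlations.** This is right. Inter-relatedness is not among the stated aims or hypotheses, no correlation is an outcome, and no decision rule uses one. A reader might infer that the trial will claim support for the combined cognitive bias hypothesis from an artefact. The documents do not say so: the Discussion cites that hypothesis as background and speaks of exploring.

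**The large rates concern the wrong pair.** A reader might take 63% to 69% as the rate for attention, interpretation and memory. It is not. Ambiguous Scenarios and Sentence Generation both measure interpretation, the effects come from 9 per arm, and no effect is given for the other two biases. For those the artefact could be small or absent.

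**The pilot reading hardly changes.** This is also right. A fall from .68 to about .59 does not make the pilot result an artefact.

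**Spread of training to other biases may be part of the question.** Pooled and within-group correlations do answer different questions. But spread is tested directly by the group comparisons under hypotheses 2 and 3. A pooled coefficient mixes it with individual association, so the two need separate labels.

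**Age and questionnaires.** It is tempting to extend the criticism to these. Training cannot change age, and the questionnaires precede training, so randomisation makes both independent of group in expectation.

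**Conclusion.** The point holds for pairs of post-training measures: bias scores with each other and with ISSA ratings. As stated, the correlations cannot distinguish linked biases from a common training effect.

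The induced correlation is modest, about .05 to .21 where training moves both measures by the amounts examined. At N = 134 that is enough to give significance in 8% to 69% of trials with no within-group association; the rate returns to 5% if one measure is unmoved. The upper end rests on imprecise pilot effects and does not describe attention or memory.

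The result assumes pooled arms, 1:1 allocation and roughly normal scores. It bears on an exploratory but declared use of the data, and leaves the primary comparison untouched.

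**What to change.** In the main study's analytic plan, state that for pairs of post-training measures (cognitive bias scores and ISSA ratings) statements on inter-relatedness will rest on correlations partialled on randomised group, that is, pooled within-group correlations. Show the per-arm coefficients descriptively, and label any pooled coefficient as including the training effect. Leave the age and questionnaire correlations as they are.

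The cost is one sentence and one degree of freedom, with no new data and no change to the sample size. The completed pilot analysis need not be redone.

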The test phase serves as a direct measure of interpretation bias, investigating whether participants interpret new ambiguous descriptions as pain-related or benign. If the modification is successful, participants in the pain modification group should make more pain-related interpretations than the benign modification group. In the first part of the test phase, 10 ambiguous descriptions were presented, each with a meaningful title. Participants were asked to complete the fragment of the final word, but this word will not disambiguate the situation. Participants were also asked a comprehension question about each description to ensure they understood the meaning. In the second part of the test phase, the title of each scenario was shown, along with four possible endings for the scenario, all of which differ slightly from the original ending. Two endings were pain-related and two were neutral. One was more relevant to the bias modification (i.e., pain-related) the other less relevant (i.e., generally negative). Participants were asked to rate the similarity of the four endings to the original scenario from 1 (very different in meaning) to 4 (very similar in meaning). Participants were instructed that although none of the endings are identical to the original description, any of them could be similar in meaning. Participants were also asked to rate how easily they could imagine themselves as the protagonist in the descriptions from 1 (not at all) to 5 (extremely) as a measure of visual imagery, which has previously been found to enhance the effectiveness of interpretation bias modification [47]. This task took approximately 20 minutes to complete.

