### Experimental paradigms

Identical to the pilot study, CBM-I training will be achieved via the Ambiguous Scenarios Task [46] modified for pain research by Jones and Sharpe [10]. Assessments of interpretation bias will be made via the test phase of the Ambiguous Scenarios Task and the Sentence Generation task. New to this main experimental study, the probe-position version of the Visual-Probe Task will be used to assess attentional biases for symbolic linguistic stimuli. Specifically, nine sensory-pain and neutral words pairs matched on length and length and Kucera–Francis written frequency [84] will be included (unique to this paradigm and not included in the Sentence Generation Task), which have been validated and used in our former research [62] (Table 4). The task will begin with eight practice trials featuring random letter strings as stimuli. This will be followed by a single block of 64 experimental trials, each of which features one sensory-pain and one neutral word pair. Each trial will begin with a fixation cross in the centre of the screen for 500ms, followed by a randomly selected word-pair presented vertically (i.e., one above the initial fixation cross, the other below) for either 500ms or 1250ms. Immediately after the disappearance of the word-pair, a visual-probe will be randomly displayed in either the upper or lower location replacing one of the former words. Participants must indicate the location of this probe as quickly as possible, using a two-button response-box (with ‘U’ and ‘L’ labels for upper and lower respectively) to provide their response. Following a randomly determined inter-trial interval of either 1000 or 1500 ms, the next trial will begin with the display of the initial fixation cross. The two stimuli presentation times will be applied in a randomised order over all trials. Each of the eight word-pairs will be presented eight times; four times for 500 ms and four times for 1250 ms. Within each exposure duration, each sensory-pain word will appear twice in the upper location and twice in the lower location. The probe location (upper or lower) will be counterbalanced across both locations, resulting in an equal number of congruent (probe replacing the sensory-pain word) and incongruent (probe replacing the neutral word) trials. This task will take approximately 15 minutes to complete. Also new to this main experimental study, a pen and paper version of the free recall task will be used to explore memory biases. Participants will unexpectedly be given two minutes to write down as many words as they can remember from the sentence generation and visual-probe tasks.

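### Visual imagery is rated after the randomised training, in the same phase as the outcome, so a group x imagery interaction cannot be read as moderation by a pre-existing trait

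*Protocol article*

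**What the plan says.** The main-study section on data reduction and analysis names two moderators of the training effect on the Ambiguous Scenarios index, to be tested by linear multiple regression: "The moderating effects of visual imagery and intolerance of uncertainty on the association between group and interpretation bias scores from the Ambiguous Scenarios Task".

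Imagery is defined only in the pilot's description of the Ambiguous Scenarios Task, in the paragraph on the test phase: "Participants were also asked to rate how easily they could imagine themselves as the protagonist in the descriptions", on a 1-5 scale, "as a measure of visual imagery, which has previously been found to enhance the effectiveness of interpretation bias modification". The same paragraph gives the purpose of that phase: "The test phase serves as a direct measure of interpretation bias, investigating whether participants interpret new ambiguous descriptions as pain-related or benign".

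The main study carries the task over ("Identical to the pilot study, CBM-I training will be achieved via the Ambiguous Scenarios Task") and processes its data as in the pilot. On order, the main-study Procedure says "Participant ID numbers will be randomly assigned to the benign or pain modification group before data collection begins". Questionnaires, pain thresholds, training and the ISSA follow. Only then comes the battery of bias tasks, where "The test phase of the Ambiguous Scenarios Task will be completed first".

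**The concern.** To say that imagery moderates the training is to say that people who differed in imagery beforehand respond differently to it. That requires a score the training could not have influenced. Here each arm first works through 60 scenario presentations with its own type of ending, and only later rates how easily it can picture itself in the test scenarios. Ease of imagining may by then reflect the allocated training, or how far the participant took up the trained reading. The outcome is scored in the same phase.

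The protocol cites earlier evidence that imagery strengthens bias modification, so a significant interaction would naturally be reported as confirming it. Without a pre-training rating, the trial could not separate that explanation from one in which the rating is partly a product of training.

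**Working it through.** **Order of measurement in the main study**

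| Step | Relevant content |
|---|---|
| 1. Allocation of participant IDs | Before data collection |
| 2. Questionnaire battery | Includes IUS-12; lists no imagery measure |
| 3. Heat and cold pain thresholds | None |
| 4. Training phase | Pain or benign endings |
| 5. ISSA (about 20 minutes) | Primary outcomes |
| 6. Test phase | Outcome index and imagery rating |

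IUS-12 precedes training; the imagery rating follows it. The main-study sections do not restate when the rating is taken, so step 6 rests on the pilot description and the carry-over statement. A rating made during training would still follow randomised exposure.

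**Inputs**
- Total N = 134 (Participants, main study). I assume 1:1 allocation, so n = 67 per arm.
- Two-sided 0.05 (Data reduction and analytic plan).
- Group effect on the index d = 1.03 (pilot, Assessments of interpretation biases).
- How imagery relates to the index: the protocol gives no figure, so every value below is an assumption.

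**The plan's own figure.** With f = 0.244, numerator df 1 and two groups, noncentral F power (λ = f²N, denominator df N − 2) is 0.7946 at N = 132 and 0.8006 at N = 134. The stated 134 is reproduced. The point here concerns timing and does not depend on it.

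**Simulation.** Let G = 0 (benign) or 1 (pain), and Y = 1.03·G + e with e ~ N(0,1), so that no pre-training trait moderates the effect. Regress Y on G, M and G×M, where M is the post-training rating, and count how often G×M is significant (4,000 trials per row). Two forms of M are used:
- Coefficient form: M = t + shift·G + c·e, where t ~ N(0,1) is a pre-training trait and c may differ by arm.
- Correlation form: M = r·s·e + √(1 − r²)·z, where z ~ N(0,1), with s = +1 in the pain arm and −1 in the benign arm.

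| Assumed behaviour of the rating | G×M significant |
|---|---|
| Unrelated to training and index | about 4% |
| Training shifts its mean by 0.5 SD only | about 5% |
| Same 0.5 SD shift, tracks index equally (c = 0.3 in both arms) | about 5% |
| Same shift, tracks index in pain arm only, c = 0.3 | 37% |
| Same shift, tracks index in pain arm only, c = 0.5 | 70% |
| Opposite directions, r = 0.1 | 20% |
| Opposite directions, r = 0.2 | 64% |
| Opposite directions, r = 0.3 | 94% |

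Using the pre-training trait t as the moderator in the coefficient-form runs gave 4% to 5% throughout.

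**Hand check by normal approximation.** The interaction compares the slope of Y on M in the two arms.
- Opposite directions, r = 0.2: slope difference 2r = 0.4; SE = √(2(1 − 0.04)/67) = 0.169; z = 0.4/0.169 = 2.36; P(Z > 1.96 − 2.36) ≈ 0.66, against 64% simulated.
- Pain arm only, c = 0.3: slope in that arm c/(1 + c²) = 0.3/1.09 = 0.275, and 0 in the other. The slope variance in the pain arm is (1 − 0.09/1.09)/(67 × 1.09) = 0.01256 and in the benign arm 1/67 = 0.01493. SE = √0.02749 = 0.166; z = 1.66; P(Z > 0.30) ≈ 0.38, against 37%.
- Equal tracking: slope difference 0, so the rate stays at 5%.

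The false-positive rate is therefore governed by the between-arm difference in slopes, not by a shift in the mean rating.

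**The case against.** The strongest objection is that the large percentages are built in. Rates of 20% to 94% arise only if the rating follows the index with opposite signs in the two arms, which itself writes a slope difference into the data. The pilot reports no imagery results, so nothing shows that this structure applies. This stands, and the range must start at about 5%. The opposite-sign case is conceivable, because the arms are trained in opposite directions on a signed index, but it is not established.

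Two stronger readings are tempting, and the documents support neither. A reader might infer that any effect of training on the rating produces a false interaction; a mean shift alone leaves the rate at about 5%. A reader might also infer that the trial's estimate of the group effect is compromised. If training shifts imagery by 0.5 SD and imagery correlates 0.3 with the index, the group coefficient in a model adjusted for imagery does fall from 1.00 to about 0.85. However, the plan tests group differences separately by t-tests and mixed ANOVAs, and nowhere says that the moderation model's coefficient will be reported as the training effect.

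The stakes are also modest: imagery moderation is neither a stated hypothesis nor a listed outcome. That limits the weight of the point but does not answer it. The protocol fixes the moderator, the outcome and when both are measured, and later analysis detail cannot turn a post-training rating into a baseline one.

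**Conclusion.** The point holds in a limited form. As written, the plan could yield a claim of moderation by imagery that the design cannot support, because the only imagery score follows the randomised training and comes from the phase that yields the outcome. The chance of a spurious interaction cannot be fixed from the protocol: it runs from about 5% to 94% over the structures examined, all assumed, with 67 per arm and no true moderation. It would be wrong to quote the upper figures as the expected error rate.

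The rating's place in the test phase is itself carried over from the pilot description, though any rating made on these scenarios during or after training raises the same difficulty. Intolerance of uncertainty is not affected. Nor are the primary ISSA comparison, the sample size or the randomisation. This is a correction worth making to a secondary analysis.

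**What to change.** In the main-study analytic plan:

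1. Restrict the moderation model to IUS-12.
2. Report the imagery rating as a post-training measure and compare it between groups.
3. Report its association with the Ambiguous Scenarios index, overall and by group, as exploratory, with no claim of moderation.

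This is a change of wording only. It applies equally to participants already tested and leaves the primary analysis untouched. The cost is the loss of the imagery moderation claim.

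A new pre-training rating is a less straightforward remedy. The protocol describes no practice scenarios for this task on which to take it, and the study's stated start is 1 June 2024, so adding one now could leave some participants without the measure.
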